### Efficacy Follow-up

Subjects who do not experience disease progression or initiate new antitumor therapy upon discontinuation of the investigational drug will continue to undergo CT/MRI scans, ECOG PS assessments, and FACT-Hep scale collections every 12 weeks (within 2 years of the first administration) or every 24 weeks (after 2 years of the first administration) until disease progression occurs, new antitumor therapy is initiated, the subject withdraws consent, is lost to follow-up, dies, or the study is terminated early (whichever occurs first). During this period, if the investigator suspects that the subject has experienced progression, an unscheduled CT/MRI examination may be conducted. Once the subject stops efficacy follow-up, the reason for termination should be recorded in the CRF form. For patients who become pregnant, all tumor assessments must be halted, regardless of whether progression has occurred.

### Survival follow-up

Survival follow-up is required after the investigator determines there is evidence of disease progression or the initiation of new antitumor therapy. Survival follow-up is conducted every 12 weeks, with telephone follow-ups to the subject or their relatives to record the subject's survival status, until the subject withdraws the ICF, is lost to follow-up, dies, or the study is terminated early (whichever occurs first).

# Evaluation indicators

## Primary efficacy evaluation indicators

- Objective response rate (ORR)

(Tumor assessment using both RECIST v1.1 and mRECIST criteria, with RECIST v1.1 as the primary criterion)

## Secondary efficacy evaluation indicators

- Based on overall survival (OS)
- Time to disease progression (TTP)
- Progression-free survival (PFS)
- Disease control rate (DCR)
- Duration of response (DOR)
- ECOG PS score temporal changes
- AFP temporal changes

(Tumor assessment using both RECIST v1.1 and mRECIST criteria, with RECIST v1.1 as the primary criterion)

## Safety evaluation indicators

- Analysis of adverse events and serious adverse events

## Definition of efficacy indicators

### Progression-free survival (PFS)

Progression-free survival time refers to the duration from randomization to tumor progression or death from any cause (with tumor progression assessed using both RECIST v1.1 and mRECIST criteria, primarily based on RECIST v1.1). If a subject is lost to follow-up during the study and no imaging evidence of progression or death is obtained, it will be recorded as censored, with the censoring time being the last follow-up date confirming no progression. For subjects whose tumor progression has not been confirmed by the database cutoff date, censoring will be based on the date of the last imaging tumor assessment. The tumor progression date is defined as the date of the first imaging-confirmed tumor progression.

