### Time to progression (time to progress, TTP)

Time to progression refers to the time from randomization to the occurrence of objective tumor progression (tumor assessment will be conducted using both RECIST v1.1 and mRECIST criteria, with RECIST v1.1 as the primary standard). If imaging progression evidence is not obtained due to loss to follow-up during the follow-up period, it will be recorded as censored, with the censoring time being the last follow-up time confirming that there was no progression.

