### Disease control rate ( disease control rate, DCR)

The disease control rate is defined as the proportion of subjects achieving the best clinical efficacy of CR, PR, or SD (with tumor assessment using both RECIST v1.1 and mRECIST criteria, primarily based on RECIST v1.1).

- - 1. **Duration of response (DOR)**

Duration of response refers to the time from the first assessment of complete response (CR) or partial response (PR) to the first assessment of disease progression (PD) or death from any cause (with tumor assessment using both RECIST v1.1 and mRECIST criteria, primarily based on RECIST v1.1).

。

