## Data Analysis Set

All observational indicators of the subjects are included in the statistical analysis. The dataset includes the Full Analysis Set (FAS), Safety Set (SS), and Per Protocol Set (PPS). Efficacy analysis will utilize both FAS and PPS, with FAS as the primary analysis set. Safety analysis will use SS.

**FAS:** Refers to the collection of all cases that have used the investigational drug at least once according to the protocol, excluding cases that have been removed; Cases that did not experience tumor progression during the observation and follow-up periods will have their tumor progression time treated as censored, with the censoring time being the most recent confirmation of no tumor progression.

**SS:** Refers to the population of subjects who have signed informed consent and have used the investigational drug at least once.

**PPS:** A subset of the FAS population, referring to all cases that have used the investigational drug according to the protocol for at least 2 weeks and meet the inclusion criteria for the FAS. Cases that have taken the drug for less than 2 weeks but have experienced radiologically confirmed disease progression within 12 weeks after starting the drug, and meet the inclusion criteria for the FAS, will also be included in the PPS. Cases in which tumor progression was not observed during the observation and follow-up periods will have their tumor progression time treated as censored, with the censoring time being the most recent confirmation of tumor non-progression.

Cases that are excluded should be retained for reference; except for cases that have previously used the drug being classified as SS, other cases (those that have not used the drug at all) will not be included in the statistical analysis.

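### The PFS censoring rule at data cutoff omits death and so contradicts the PFS definition in the same section

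*Protocol*

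**What the plan says.** Section 7.4.1 of the protocol opens with the definition: "Progression-free survival time refers to the duration from randomization to tumor progression or death from any cause". Two censoring rules follow.

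- Loss to follow-up, which leads to censoring: "If a subject is lost to follow-up during the study and no imaging evidence of progression or death is obtained, it will be recorded as". An observed death takes a patient out of this rule.
- Data cutoff: "For subjects whose tumor progression has not been confirmed by the database cutoff date, censoring will be based on the date of the last", where the sentence goes on to name the scan. The only condition is that progression has not been confirmed. Death is not mentioned.

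Three other places bear on the point.

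- Section 7.4.2 (OS) applies its cutoff censoring only to patients who are still alive.
- Section 7.4.3 defines TTP without death: "Time to progression refers to the time from randomization to the occurrence of objective tumor progression". For patients lost to follow-up it censors "with the censoring time being the last follow-up time confirming that there was no progression".
- Section 10.1, in describing the full analysis set, says: "Cases that did not experience tumor progression during the observation and follow-up periods will have their tumor progression time treated as censored". It repeats the rule for the per-protocol set. Neither sentence names PFS or mentions death.

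Section 10.3.2 summarises PFS and TTP by Kaplan-Meier medians with 95% confidence intervals.

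**The concern.** A patient who dies with no scan showing progression fits the cutoff sentence word for word, because that patient's progression was never confirmed. Take stable disease at weeks 6 and 12 and death at week 16. The definition gives an event at week 16; the cutoff sentence gives censoring at week 12. Two programmers could code this record differently and both cite section 7.4.1.

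Death before documented progression is the outcome that separates PFS from TTP. If such deaths are censored, PFS loses that content. The usual effect on the reported median is in the favourable direction, and a single-arm trial has no control arm in which the same error would show.

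**Working it through.** The protocol gives no expected PFS, event count or power, and fixes the sample at 30 (section 3.2). There is no planned figure to reproduce, so the check compares the two readings of the rule.

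**Inputs**

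- Sample size 30: section 3.2.
- Scans every 6 weeks on treatment: section 6.3.
- True median PFS m = 10.5 months: an assumption, taken from the similar triplet trial cited in section 1.5.
- Share d of first PFS events that are deaths without imaging progression: not in the document, so a range is shown.
- Accrual over 12 months and 36 months in total: assumptions for the simulation. The synopsis gives a study duration of 3 years.

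**Closed form.** With independent exponential times, the total hazard is h = ln 2 / m and the progression hazard is (1 − d)h. If deaths are censored, only the progression hazard is estimated, so the median becomes ln 2 / ((1 − d)h) = m / (1 − d).

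- d = 5%: 10.5 / 0.95 = 11.1 months (+5%)
- d = 10%: 10.5 / 0.90 = 11.7 months (+11%)
- d = 15%: 10.5 / 0.85 = 12.4 months (+18%)
- d = 20%: 10.5 / 0.80 = 13.1 months (+25%)
- d = 30%: 10.5 / 0.70 = 15.0 months (+43%)

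**Simulation.** 4,000 trials of 30 patients, with progression detected at the next 6-weekly scan. Each trial was analysed twice: deaths as events on their date, and deaths censored at the last scan. Medians are the middle value over the runs, in months.

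| Share d | Mean deaths without progression | Median, deaths as events | Median, deaths censored | Runs with higher median | Runs unchanged |
|---|---|---|---|---|---|
| 5% | 1.4 | 11.05 | 11.05 | 41% | 59% |
| 10% | 2.7 | 11.05 | 12.43 | 64% | 36% |
| 15% | 4.0 | 11.05 | 12.43 | 80% | 20% |
| 20% | 5.4 | 11.05 | 13.81 | 88% | 12% |
| 30% | 8.0 | 10.79 | 15.19 | 97% | 3% |

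The baseline of about 11 rather than 10.5 months reflects progression being recorded only at scans.

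**Direction.** The censored version never gave the lower median. When every patient is scanned on the same grid until death, both analyses have the same patients at risk at each scan, and counting deaths only adds steps down. This argument needs scans to continue. If they stop long before death, a patient censored at the last scan leaves the risk set early, whereas a patient whose death is counted stays at risk for longer. Counting that death can then raise the curve in between.

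**The case against.** The strongest reply is that the definition comes first and already makes death an event. Censoring rules ordinarily apply to patients without an event, so a patient who died would never reach the cutoff sentence. The rest of the protocol agrees: the loss-to-follow-up rule excludes observed deaths, DOR runs "to the first assessment of disease progression (PD) or death from any cause", and section 8.8.8 treats death as an efficacy endpoint. Nothing states that deaths are censored for PFS. This stands as a likely account of the intention, and the unseen SAP may settle the coding. It does not remove the conflict: the protocol states a rule, and the rule's condition covers the deaths that the definition counts.

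A reader might infer more than the document supports:

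- **That the plan is to censor deaths and the median will be overstated.** This depends on literal application and on how many such deaths occur. With one or two among 30 patients the median may not move.
- **That PFS and TTP become numerically identical.** Only the event sets would coincide. The censoring dates are worded differently, and section 7.4.3 has no rule of its own for cutoff or for deaths.
- **That section 10.1 confirms the censoring of deaths.** Its sentences concern tumor progression time, which most naturally means TTP, where leaving death out is correct.
- **That the 15.1% of fatal treatment-emergent events at donafenib 0.2 g in section 1.3.2.2 gives the share d.** It is a proportion of patients on monotherapy, not of first PFS events, and that section does not say how many of those deaths preceded progression.

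**Conclusion.** The point holds as an internal contradiction in section 7.4.1: the same death is an event under the definition and censored under the cutoff sentence. The alive condition used for OS, and the mention of death in the loss-to-follow-up rule, suggest that the omission is an oversight.

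If the sentence is applied literally, PFS takes the event set of TTP. While scans continue to death, its median is then biased upward or unchanged. The closed-form increase runs from 5% to 25% for shares of 5% to 20%. These figures rest on independent exponential times, a median borrowed from another regimen, and an assumed share; they show scale and are not predictions for this trial.

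The consequence is limited. PFS is a secondary, descriptive endpoint, so the primary ORR analysis, the sample size and any testing are untouched. The correction is still worth making before database lock, because it concerns a reported endpoint and costs almost nothing.

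**What to change.** Replace the cutoff sentence in section 7.4.1 with: *Subjects alive and without documented progression at the database cutoff are censored at the date of the last imaging tumor assessment; death without prior documented progression is a PFS event on the date of death.*

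In section 10.1, state that the two sentences on tumor progression time apply to TTP and do not censor deaths for PFS.

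State with it how deaths after new antitumor therapy, or long after the last scan, are handled. Under section 6.5.2 scans stop once new therapy starts, and section 6.5.3 then follows survival only. Without such a rule, the new sentence would count a late death on its own date as a PFS event, which can lengthen PFS for that patient.

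The cost is wording only. Survival status is already collected every 12 weeks (section 6.5.3). The reported median PFS may be shorter than under the literal reading.

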### Overall survival （overall survival, OS ）

The time from the date of enrollment to the date of death from any cause. If the subject is still alive at the database cutoff date, censoring will be performed at the last survival follow-up date in the database.

### Time to progression (time to progress, TTP)

Time to progression refers to the time from randomization to the occurrence of objective tumor progression (tumor assessment will be conducted using both RECIST v1.1 and mRECIST criteria, with RECIST v1.1 as the primary standard). If imaging progression evidence is not obtained due to loss to follow-up during the follow-up period, it will be recorded as censored, with the censoring time being the last follow-up time confirming that there was no progression.

### Objective response rate (objective response rate, ORR)

The objective response rate is defined as the proportion of subjects with the best overall response confirmed as CR or PR (using both RECIST v1.1 and mRECIST criteria for tumor assessment, with RECIST v1.1 as the primary criterion). In calculating ORR, any partial or complete responses confirmed prior to any other antitumor therapy are counted as responses, regardless of how many assessments were missed prior to the response. When the best overall response of subjects is 'unknown' or 'not assessed', it is considered as non-response when estimating ORR.

### Disease control rate ( disease control rate, DCR)

The disease control rate is defined as the proportion of subjects achieving the best clinical efficacy of CR, PR, or SD (with tumor assessment using both RECIST v1.1 and mRECIST criteria, primarily based on RECIST v1.1).

- - 1. **Duration of response (DOR)**

Duration of response refers to the time from the first assessment of complete response (CR) or partial response (PR) to the first assessment of disease progression (PD) or death from any cause (with tumor assessment using both RECIST v1.1 and mRECIST criteria, primarily based on RECIST v1.1).

。

# Safety Monitoring and Reporting

## Adverse Events (AE)

According to the International Conference on Harmonisation (ICH) Technical Requirements for Registration of Pharmaceuticals for Human Use, 'Good Clinical Practice' (GCP), an AE refers to any unfavorable sign, symptom, or medical event that occurs after obtaining the patient's signed informed consent, regardless of whether there is a causal relationship with the treatment. Therefore, an AE may be any of the following:

1. An AE may be any unfavorable and unintended sign (including abnormal laboratory findings), symptom, or disease (new or exacerbated) that occurs after the use of a certain therapeutic drug and has a temporal relationship with the drug use;
2. Any new disease or exacerbation of pre-existing conditions (manifestations, frequency, or severity of existing conditions worsening);
3. Recurrence of intermittent disease conditions (such as headaches) that were not present during the baseline period;
4. Any deterioration in laboratory test results or other clinical examinations (e.g., ECG) that is accompanied by clinical symptoms, or that leads to changes in the study treatment or concomitant medication, or that results in the termination of the investigational drug treatment;
5. Adverse events (AEs) related to the interventions specified in the study protocol;
6. Signs, symptoms, or clinical sequelae suspected to be caused by an overdose of the investigational drug or concomitant medication (overdose itself is not reported as an AE/SAE).

**Events that do not meet the definition of an AE include:**

1. Medical or surgical procedures (e.g., endoscopy, appendectomy); the conditions leading to these procedures should be recorded as AEs;
2. Conditions of hospitalization that did not result in adverse medical events (due to social insurance and/or convenience hospitalization);
3. Planned hospitalization required by the protocol (e.g., for the use of the investigational drug);
4. Expected day-to-day fluctuations of pre-existing diseases or conditions present or detected at the start of the study, but without exacerbation;
5. Expected progression, signs, or symptoms of the disease/disorder being studied, unless the severity of the subject's condition exceeds expectations or progresses more rapidly.

Adverse signs, symptoms, or medical conditions that existed at the time of signing the informed consent form should be recorded as medical history.

## Serious Adverse Events (SAE)

Meets any of the following criteria:

1. Results in death (i.e., AE causes or leads to death);
2. Is life-threatening (i.e., the investigator believes that the AE places the patient at immediate risk of death);

Note: The term 'life-threatening' refers to the risk of death at the time of the event, and does not imply that a more severe event would lead to death.

1. Results in permanent or significant disability or functional impairment;

Note: The term 'disability' refers to a severe impairment of an individual's ability to perform normal life functions. This definition does not include clinically insignificant events, such as simple headaches, nausea, vomiting, diarrhea, influenza, and accidental injuries (e.g., ankle sprains), which may affect daily functioning but do not result in a significant loss of function.

1. Causing congenital malformations/birth defects;
2. Requires hospitalization or prolongation of current hospitalization ;

Note: Generally speaking, hospitalization refers to a patient being observed in a hospital or emergency department (typically at least overnight) and/or receiving treatment that is not suitable for a doctor's office or outpatient department.

Hospitalization for the following reasons is not reported as an AE, but the reason for hospitalization must be clearly documented in the medical record:

1. Planned hospitalization as specified in the study protocol (e.g., for administration of the investigational drug, or for efficacy assessment of this study);
2. Routine treatment or monitoring for the study indication;
3. Hospitalization solely due to related tumor progression;
4. Hospitalization due to pre-existing conditions, but must meet all of the following criteria:
   - - Hospitalization planned prior to the study, or hospitalization for elective surgery due to predictable disease progression during the study;
     - Subjects did not experience any AEs or disease progression.
5. Social reasons and treatment delays in the absence of deterioration in the patient's general condition.

The following hospitalization situations will not be considered SAEs but should be reported as AEs:

1. Subjects hospitalized due to the need for outpatient medical care outside of normal clinic hours.
2. Other important medical events that require medical and scientific judgment to determine whether expedited reporting is necessary, such as important medical events that may not immediately threaten life, result in death, or require hospitalization, but if medical measures are needed to prevent one of the above situations from occurring, are typically considered serious. For example, important treatments in the emergency room or allergic bronchospasm occurring at home, cachexia or seizures not requiring hospitalization, and the development of drug dependence or addiction, etc.
3. SAE as defined in the protocol:
4. Potential drug-induced liver injury, including elevated ALT or AST levels, accompanied by elevated bilirubin levels or clinical jaundice, as specifically defined in the Hais' criteria (see Section 8.8.7 for details).
5. AE caused by drug overdose, regardless of the CTCAE grading level.

If tumor progression (including fatal outcomes) is recorded using appropriate methods (such as according to the mRECIST criteria for solid tumors), it is not reported as a serious adverse event.

In cases where treatment is based on outpatient emergency visits that do not result in hospitalization and the events do not meet any of the SAE definitions provided above, they are not reported as serious adverse events.

The terms 'serious' and 'severe' are not synonymous; 'severity' and 'seriousness' are also not synonymous. Severity refers to the intensity of the AE (as determined by CTCAE v5.0; see [Section 8.6](#_不良事件严重程度评价) ); The medical significance of the event itself may be relatively minor (for example, severe headache with no other findings).

## Special adverse event management for donafenib tablets

### Hand-foot syndrome ( HFSR)

**Definition of HFSR:** It refers to the numbness or erythema of the palms and soles, which is a type of skin toxicity that is more pronounced in areas under pressure or stress. It can occur in cancer patients undergoing chemotherapy or molecular targeted therapy. The characteristics of HFSR include numbness, sensory loss, abnormal sensations, tingling, absence of pain or pain, skin swelling, erythema, desquamation, fissures, indurated blisters, and severe pain, among others.

**HFSR grading:**

- Grade 1: Numbness/tingling/abnormal sensations in the hands and/or feet, painless swelling or erythema, and/or discomfort that does not affect normal activities;
- Grade 2: Painful erythema and swelling in the hands and/or feet and/or discomfort that affects the patient's daily activities;
- Grade 3: Moist desquamation, ulcers, blisters, or severe pain in the hands and/or feet and/or severe discomfort that prevents the patient from working or performing daily activities. Pain is intense, with loss of skin function, and is relatively rare;

**Symptomatic treatment and management of HFSR:** Implement necessary supportive care, including: enhancing skin care, maintaining skin cleanliness, avoiding secondary infections; avoiding pressure or friction; Use of emollients or lubricants, vitamin ointments, and topically applied lotions or lubricants containing urea and corticosteroids; antifungal or antibiotic treatment topically as needed.

